# 1. Title Page

DISCLAIMER: This protocol is based on the research question and design from a real study protocol under development. It has been anonymized due to the ongoing nature of the work. To reflect the realistic situation of a developing protocol with multiple versions after input from various stakeholders, at several points in the document, the protocol states that a decision is “to be discussed” or “to be determined” indicating that it will be further developed in a later version of the protocol. Abbreviated responses are provided to illustrate how to use the protocol template, however appendices were not prepared for this example protocol.

| Title | Drug A/B combination as a second- or third-line treatment of patients with biomarker Y+ metastatic cancer compared to usual standard care |
| --- | --- |
| Research question & Objectives | The objective is to evaluate the comparative effectiveness and cost-effectiveness of Drug A/B as a second- or third-line treatment of patients with biomarker Y+ metastatic colorectal cancer compared to standard care |
| Protocol version | V1 |
| Last update date | 2021-10-26 |
| Contributors | **Primary investigator contact information:**  [contact]  **Contributor names:**  [name]  [name] |
| Study registration | **Site:** Health Technology Assessment of Anonymous Country  **Identifier:** To Be Determined |
| Sponsor | **Organization:** Health Technology Assessment of Anonymous Country  **Contact:** [contact] |
| Conflict of interest | n/a |

Table of contents

[1. Title Page 1](#_Toc102631400)

[2. Abstract 3](#_Toc102631401)

[3. Amendments and updates 4](#_Toc102631402)

[4. Milestones 5](#_Toc102631403)

[Table 1 Milestones 5](#_Toc102631404)

[5. Rationale and background 5](#_Toc102631405)

[6. Research question and objectives 6](#_Toc102631406)

[Table 2 Primary and secondary objectives and research questions 6](#_Toc102631407)

[7. Research methods 10](#_Toc102631408)

[7.1. Study design 10](#_Toc102631409)

[7.2. Study design diagram 11](#_Toc102631410)

[7.3. Setting 11](#_Toc102631411)

[7.3.1 Context and rationale for definition of time 0 (and other primary time anchors) for entry to the study population 11](#_Toc102631412)

[Table 3 Operational Definition of Time 0 (index date) and other primary time anchors 11](#_Toc102631413)

[7.3.2 Context and rationale for study inclusion criteria: 12](#_Toc102631414)

[Table 4. Operational Definitions of Inclusion Criteria 12](#_Toc102631415)

Drug A has a marketing authorisation in combination with Drug B 'for the treatment of adult patients with metastatic [organ]cancer with a biomarker Y+ mutation, who have received prior systemic therapy. There are a number of gaps identified in terms of the effectiveness and cost-effectiveness of Drug A/B combination in clinical practice compared to standard of care (SoC). Specifically:

- To what extent are the patients who are treated with Drug A/B in clinical practice similar to the patients included in the pivotal trial ACRONYM RCT?
- Do we know whether the relative effectiveness of Drug A/B compared to SoC in clinical practice is similar to relative effectiveness measured in the ACRONYM trial?
- It is unknown to which extent Drug A/B affects the quality of life of patients measured by generic (EQ-5D) and disease-specific (EORTC QLQ-CRXX and EORTC QLQ-CXY) compared to SoC
- There is no information on the cost-effectiveness of Drug A/B compared to SoC based on data from clinical practice.

This study aims to address the gaps in knowledge in [anonymous country]. The outcomes of the study may influence the guidance for use and reimbursement of Drug A/B in the [anonymous country] clinical practice.

The study will use the XYZ Data Registry in [anonymous country]. The registry includes longitudinal electronic health records, insurance claims, death records, and patient reported outcomes for a national registry of patients with metastatic [organ] carcinoma. The data in the registry was specifically collected to address the research objectives of this protocol. The quality of the registry has been assessed and found to be high using the REQUEST tool, and detailed documentation about the data sources, linkage, provenance, quality assurance, and financing (www.redactedlink.com).

3. Amendments and updates

| **Version date** | **Version number** | **Section of protocol** | **Amendment or update** | **Reason** |
| --- | --- | --- | --- | --- |
| 2021-10-26 | 1 | All | Preparation Research Protocol | Draft in preparation |
|  |  |  |  |  |
|  |  |  |  |  |
|  |  |  |  |  |

1. Milestones

#### Table 1 Milestones

| **Milestone** | **Date** |
| --- | --- |
| Feasibility counts | 2022-01-01 |
| Draft 1 of protocol complete | 2022-03-01 |
| Registration of protocol and lock/freeze data | 2022-03-01 |
| Study progress report 1 | 2022-09-01 |
| Study progress report 2 (interim analysis) | 2023-03-01 |
| Final report of study results | 2023-09-01 |

1. Rationale and background

**What is known about the condition:** Metastatic [organ]cancer with a biomarker Y+ mutation is a rare type of cancer. It is associated with a poorer prognosis and has a greater risk of recurring than [organ]cancer without the mutation. There has been little improvement in survival for biomarker Y mutation-positive cancer despite overall improvements in survival for this type of cancer suggesting an unmet medical need. At the moment there are currently no effective treatments for this type of [organ]cancer. Drug A in combination with Drug B may represent a step change in treatment.

**What is known about the exposure of interest:** Drug A has a marketing authorisation in combination with Drug B ‘for the treatment of adult patients with metastatic [organ]cancer with a biomarker Y+ mutation, who have received prior systemic therapy' based on a pivotal clinical trial ACRONYM RCT.

**Gaps in knowledge:** There are number of gaps identified in terms of the effectiveness and cost-effectiveness of Drug A/B combination in clinical practice compared to standard of care (SoC):

- To which extent are the patients who are treated with Drug A/B in clinical practice similar to the patients included in the pivotal trial ACRONYM RCT?
- Do we know whether the relative effectiveness of Drug A/B compared to SoC in clinical practice is similar to relative effectiveness measured in the ACRONYM RCT trial?
- It is unknown to which extent Drug A/B affects the quality of life of patients measured by generic (EQ-5D) and disease-specific (EORTC QLQ-CRXXand EORTC QLQ-CXY) compared to SoC
- There is no information on the cost-effectiveness of Drug A/B compared to SoC based on data from clinical practice.

**What is the expected contribution of this study?** This study is aiming to address the gaps in knowledge in [anonymous country]. The outcomes of the study may influence the guidance for coverage and reimbursement of Drug A/B in the [anonymous country] clinical practice.

1. Research question and objectives

#### Table 2 Primary and secondary objectives and research questions

1. **Primary objective and research question**

| **Objective:** | To compare overall survival (OS) in patients > 18 years with metastatic [organ]carcinoma with a biomarker Y+ mutation who have shown progression after first line treatment and have indicated informed consent for longitudinal observational data collection as part of the XYZ Registry and are treated with a combination of Drug A and Drug B compared to controls who are treated with standard care for a period of a maximum of 2 years (or 4 years). Comparator patients will be included retrospectively as well prospectively. |
| --- | --- |
| **Hypothesis:** | Overall survival will be improved with Drug A and Drug B compared to standard of care. |
| **Population *(mention key inclusion-exclusion criteria):*** | Patients with biomarker Y+ positive metastatic [organ] cancer who progressed after at least of one line of treatment |
| **Exposure:** | Initiation of Drug A in combination with Drug B |
| **Comparator:** | Standard of care. In [anonymous country], SoC second line therapy is Drug C or in third line the SoC is Drug D. There will be 2 comparator arms. One will be initiation of Drug C or Drug D using concurrent years of data with the exposure arm. The other comparator group will be initiatiors of Drug C or Drug D using historical controls from years of data prior to availability of Drug A/B. |
| **Outcome:** | Overall Survival (OS) |
| **Time *(when follow up begins and ends):*** | Follow up from day after initiation of therapy until the first of outcome, discontinuation, add/switch therapy, disenrollment, end of study period, nursing home admission, death, progression of therapy, others to be discussed. |
| **Setting:** | Outpatient care |
| **Main measure of effect:** | Hazard Ratio (to be discussed). |

1. **Secondary objective 1 and research question**

| **Objective:** | To compare progression-free survival (PFS) and/or time to treatment failure (TTTF) in patients > 18 years with metastatic [organ] carcinoma with a biomarker Y+ mutation who have shown progression after first line treatment and have indicated informed consent for longitudinal observational data collection as part of the XYZ Registry and are treated with a combination of Drug A/B compared to patients who are treated with standard care for a period of a maximum of 2 years (or 4 years). Comparator patients will be included retrospectively as well prospectively |
| --- | --- |
| **Hypothesis:** | Progression-free survival (PFS) and/or time to treatment failure (TTTF) will be improved with Drug A and Drug B compared to standard of care. |
| **Population *(mention key inclusion-exclusion criteria):*** | Patients with biomarker Y+ positive metastatic [organ] cancer who progressed after at least of one line of treatment |
| **Exposure:** | Initiation of Drug A in combination with Drug B |
| **Comparator:** | Standard of care. In [anonymous country], SoC second line therapy is Drug C or in third line the SoC is Drug D. There will be 2 comparator arms. One will be initiation of Drug C or Drug D using concurrent years of data with the exposure arm. The other comparator group will be initiatiors of Drug C or Drug D using historical controls from years of data prior to availability of Drug A/B. |
| **Outcome:** | Progression-free survival (PFS) and/or time to treatment failure (TTTF) |
| **Time *(when follow up begins and ends):*** | Follow up from day after initiation of therapy until the first of outcome, discontinuation, add/switch therapy, disenrollment, end of study period, nursing home admission, death, progression of therapy, others to be discussed. |
| **Setting:** | Outpatient care |
| **Main measure of effect:** | Hazard Ratio (to be discussed). |

1. **Secondary objective 3 and research question**

| **Objective:** | To compare generic health-related quality of life (HRQoL) (using EQ-5D) and disease-specific HRQoL (using EORTC-QLQ-C30) in patients > 18 years with metastatic [organ]carcinoma with a biomarker Y+ mutation who have shown progression after first line treatment and have indicated informed consent for longitudinal observational data collection as part of the XYZ Registry and are treated with a combination of Drug A/B compared to patients who are treated with standard care for a period of a maximum of 2 years (or 4 years). Comparator patients will be included retrospectively as well prospectively. |
| --- | --- |
| **Hypothesis:** | Generic health-related quality of life (HRQoL) (using EQ-5D) and disease-specific HRQoL (using EORTC-QLQ-C30) will be improved with Drug A and Drug B compared to standard of care. |
| **Population *(mention key inclusion-exclusion criteria):*** | Patients with biomarker Y+ positive metastatic [organ] cancer who progressed after at least of one line of treatment |
| **Exposure:** | Initiation of Drug A in combination with Drug B |
| **Comparator:** | Standard of care. In [anonymous country], SoC second line therapy is Drug C or in third line the SoC is Drug D. There will be 2 comparator arms. One will be initiation of Drug C or Drug D using concurrent years of data with the exposure arm. The other comparator group will be initiatiors of Drug C or Drug D using historical controls from years of data prior to availability of Drug A/B. |
| **Outcome:** | Generic health-related quality of life (HRQoL) (using EQ-5D) and disease-specific HRQoL (using EORTC-QLQ-C30) |
| **Time:** | Follow up from day after initiation of therapy until the first of outcome, discontinuation, add/switch therapy, disenrollment, end of study period, nursing home admission, death, progression of therapy, others to be discussed. |
| **Setting:** | Outpatient care |
| **Main measure of effect:** | (to be discussed) |

1. **Secondary objective 3 and research question**

| **Objective:** | To compare toxicity and/or adverse effects in patients > 18 years with metastatic [organ]carcinoma with a biomarker Y+ mutation who have shown progression after first line treatment and have indicated informed consent for longitudinal observational data collection as part of the XYZ Data Registry and are treated with a combination of Drug A/B compared to patients who are treated with standard care for a period of a maximum of 2 years (or 4 years). Comparator patients will be included retrospectively as well prospectively. |
| --- | --- |
| **Hypothesis:** | Toxicity and/or adverse effects will be no different with Drug A and Drug B compared to standard of care. |
| **Population *(mention key inclusion-exclusion criteria):*** | Patients with biomarker Y+ positive metastatic [organ] cancer who progressed after at least of one line of treatment |
| **Exposure:** | Initiation of Drug A in combination with Drug B |
| **Comparator:** | Standard of care. In [anonymous country], SoC second line therapy is Drug C or in third line the SoC is Drug D. There will be 2 comparator arms. One will be initiation of Drug C or Drug D using concurrent years of data with the exposure arm. The other comparator group will be initiatiors of Drug C or Drug D using historical controls from years of data prior to availability of Drug A/B. |
| **Outcome:** | Toxicity and/or adverse effects |
| **Time:** | Follow up from day after initiation of therapy until the first of outcome, discontinuation, add/switch therapy, disenrollment, end of study period, nursing home admission, death, progression of therapy, others to be discussed. |
| **Setting:** | Outpatient care |
| **Main measure of effect:** | Hazard ratio (to be discussed) |

1. **Secondary objective 4 and research question**

| **Objective:** | To compare resource use in patients > 18 years with metastatic [organ]carcinoma with a biomarker Y+ mutation who have shown progression after first line treatment and have indicated informed consent for longitudinal observational data collection as part of the XYZ Data Registry and are treated with a combination of Drug A/B compared to patients who are treated with standard care for a period of a maximum of 2 years (or 4 years). Comparator patients will be included retrospectively as well prospectively |
| --- | --- |
| **Hypothesis:** | Resource utilization will be reduced with Drug A and Drug B compared to standard of care. |
| **Population *(mention key inclusion-exclusion criteria):*** | Patients with biomarker Y+ positive metastatic [organ] cancer who progressed after at least of one line of treatment |
| **Exposure:** | Initiation of Drug A in combination with Drug B |
| **Comparator:** | Standard of care. In [anonymous country], SoC second line therapy is Drug C or in third line the SoC is Drug D. There will be 2 comparator arms. One will be initiation of Drug C or Drug D using concurrent years of data with the exposure arm. The other comparator group will be initiatiors of Drug C or Drug D using historical controls from years of data prior to availability of Drug A/B. |
| **Outcome:** | Resource utilization |
| **Time:** | Follow up from day after initiation of therapy until the first of outcome, discontinuation, add/switch therapy, disenrollment, end of study period, nursing home admission, death, progression of therapy, others to be discussed. |
| **Setting:** | Outpatient care |
| **Main measure of effect:** | Descriptive statistics (to be discussed) |

1. Research methods
   1. Study design

**Research design (e.g. cohort, case-control, etc.):** New user active comparator cohort study

**Rationale for study design choice:** In order compare the new treatment (Drug A/B) with standard of care (SoC), patients need to be followed from start treatment until censoring (death, progression, treatment failure, end of follow-up). Use of this design will help prevent time related biases such as depletion of susceptible, immortal time bias and adjustment for causal intermediates.

- 1. Study design diagram

[figure not shown]

- 1. Setting

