#### Table 8. Operational Definitions of Follow Up

|  |  |  |  |
| --- | --- | --- | --- |
| **Follow up start** | Day 1 |  |  |
| **Follow up end^1^** | **Select all that apply** |  | **Specify** |
| **Date of outcome** | Yes |  | See Table 5 |
| **Date of death** | Yes |  | Discharged dead or registry recorded death, whichever came 1st |
| **End of observation in data** | Yes |  | Allow 30 day gaps in enrolment |
| **Day X following index date**  *(specify day)* | Yes |  | Day 365 |
| **End of study period**  (specify date) | Yes |  | 30-Sep-15 |
| **End of exposure**  *(specify operational details,*  *e.g. stockpiling algorithm, grace period)* | Yes |  | **Stockpiling algorithm:** If refill occurs before end of days supply, count overlapping days at the end of the subsequent dispensing’s day supply.  **Grace period:** Bridge gaps of ≤30 days between dispensation + days supply and refill. Add 30 days to last dispensation + days supply in a treatment episode. |
| **Date of add to/switch from exposure**  *(specify algorithm)* | Yes |  | Date that patient in exposed group is dispensed comparator drug or vice versa |
| **Other date** *(specify)* | Yes |  | Nursing home admission |

^1^ Follow up ends at the first occurrence of any of the selected criteria that end follow up.

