#### Table 10. Primary, secondary, and subgroup analysis specification

1. **Primary analysis**

| **Hypothesis:** | Exposure to Drug A/B increases risk of death relative to SoC comparators with the lower bound of the 95% confidence interval for the hazard ratio above 1.0. |
| --- | --- |
| **Exposure contrast:** | Exposure, comparator 1 (concurrent) |
| **Outcome:** | Death |
| **Analytic software:** | SAS 9.4: PHREG, PROC LOGISTIC, Pharmacoepi Toolbox nearest neighbor matching macro (http://www.drugepi.org/dope-downloads/) |
| **Model(s):**  ***(provide details or code)*** | *Outcome model:* Cox proportional hazards  followuptime*status(0) = exposure  *Propensity score model*: logistic regression  Exposure = Risk factors to be determined |
| **Confounding adjustment method** | ***Name method and provide relevant details, e.g. bivariate, multivariable, propensity score matching (specify matching algorithm ratio and caliper), propensity score weighting (specify weight formula, trimming, truncation), propensity score stratification (specify strata definition), other.*** |
|  | We will use logistic regression to estimate a propensity score using covariates that will be determined and recorded in an updated protocol before conducting inferential analysis. We will use this propensity score to nearest-neighbor match with a caliper of 0.2 standard deviations on the logit scale of the propensity score using the nearest neighbor algorithm from the Pharmacoepi Toolbox. |
| **Missing data methods** | ***Name method and provide relevant details, e.g. missing indicators, complete case, last value carried forward, multiple imputation (specify model/variables), other.*** |
|  | Patients with missing or unknown sex will be excluded. Multiple imputation will be used to impute missing data on health related quality of life at baseline. We assume that if no relevant claims diagnoses/procedures are present in the registry data, that the patient does not have the condition/procedure. |
| **Subgroup Analyses** | ***List all subgroups*** |
|  | 1. 2^nd^ vs 3^rd^ line of therapy |

1. **Secondary Analysis 1**

| **Hypothesis:** | Exposure to Drug A/B increases risk of progression free survival relative to SoC comparators with the lower bound of the 95% confidence interval for the hazard ratio above 1.0. |
| --- | --- |
| **Exposure contrast:** | Exposure, comparator 1 (concurrent) |
| **Outcome:** | Progression free survival |

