#### Table 12. Metadata about data sources and software

|  | **Data 1** | **Data 2** |
| --- | --- | --- |
| **Data Source(s):** | XYZ Data Registry (concurrent/prospective) | XYZ Data Registry (historical) |
| **Study Period:** | Jan 1, 2021- Dec 31, 2022 | Jan 1, 2019- Dec 31, 2020 |
| **Eligible Cohort Entry Period:** | Jan 1, 2021- Dec 31, 2022 | Jan 1, 2019- Dec 31, 2020 |
| **Data Version (or date of last update):** | V2.0 – V5.0 | V1.0 |
| **Data sampling/extraction criteria:** | All patients > 18 years with metastatic [organ] carcinoma with a biomarker Y+ mutation who have shown progression after first line treatment and are treated with a combination of Drug A/B or with standard care | All patients > 18 years with metastatic [organ] carcinoma with a biomarker Y+ mutation who have shown progression after first line treatment and are treated with standard care |
| **Type(s) of data:** | Patient registry data including linked electronic health records, insurance claims, death, and patient reported outcomes | Patient registry data including linked electronic health records, insurance claims, death, and patient reported outcomes |
| **Data linkage:** | Linked based on universal patient identifier in [anonymous country] | Linked based on universal patient identifier in [anonymous country] |
| **Conversion to CDM*:** | n/a | n/a |
| **Software for data management:** | SAS 9.4, My SQL 15.0.2000.5 | SAS 9.4, My SQL 15.0.2000.5 |

*CDM = Common Data Model

- 1. Data management

The research team operates a secure, state-of-the-art, computing facility. The computer cluster is Linux-based and offers SAS 9.4, Stata 15.1, and R. The data center is a secure facility that houses both our computing environment as well as clinical systems and electronic medical records for several large hospitals in WA. Entry into the computer room requires passing through staffed building security, a successful palm scan, and then passing through staffed computer room security. The research machines are connected to the networking backbone with 10 gigabit-per-second fiber links. Network security is overseen by Information Security, who apply the same standards used for the hospitals electronic medical records systems to the research teams data. All data are transmitted to programmers' workstations in an encrypted state. Backups are created using 256-bit AES encryption, the current Department of Defense standard for data security, and are stored in a locked facility.

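### If registry consent is required and can follow drug start, counting follow-up from Day 1 creates immortal time; the protocol does not say who must consent or when

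*Protocol*

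**What the plan says.** Every objective in Table 2 of the protocol describes patients who "have indicated informed consent for longitudinal observational data collection as part of the XYZ Registry" (the registry's name varies slightly) and adds: "Comparator patients will be included retrospectively as well prospectively". The Time row of the same table reads "Follow up from day after initiation of therapy until the first of outcome", and Table 8 fixes Day 1 as the start of follow-up. Neither provides for later entry.

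Table 2 defines two SoC arms, one concurrent and one made up of "historical controls from years of data prior to availability of Drug A/B". Table 12 gives the historical entry period as "Jan 1, 2019- Dec 31, 2020" and the concurrent one as 2021 to 2022. The primary analysis and secondary analysis 1 in Table 10 compare Drug A/B with the concurrent arm only.

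Consent appears in neither Table 4 nor Table 5. The extraction criteria in Table 12 take all patients who meet the clinical conditions. Section 7.1 says of the cohort design: "Use of this design will help prevent time related biases such as depletion of susceptible, immortal time bias". The limitations in Section 8 cover unmeasured variables, lack of randomisation and informative censoring, but not selection by survival to consent.

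**The concern.** A patient who consents after starting treatment must be alive to do so. If consent is needed for inclusion, anyone who dies between drug start and consent never enters the data. Those who do enter carry an interval in which death was impossible, and the stated follow-up rule counts it as time at risk. The primary outcome is overall survival and the planned effect is small (HR 0.90, Section 7.9), so a modest amount of such time in one arm could hide the effect or exaggerate it. The result may inform coverage and reimbursement (Section 5). The new-user design named in Section 7.1 does not remove this problem, because the problem comes from the timing of consent and not from prior drug use.

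**Working it through.** **The plan's own figure.** Section 7.9 gives 5,000 exposed patients, 1:1 matching, 35% deaths in one year and more than 80% power for HR 0.90. The significance level is not stated there; two-sided 0.05 is inferred from the 95% interval in Table 10. Power = Φ(|ln HR| × √(events/4) − 1.96).
- 35% deaths in both arms: 10,000 × 0.35 = 3,500 events; 0.1054 × √875 − 1.96 = 1.16; power 87.6%.
- 35% in SoC and HR 0.90 in Drug A/B: about 3,356 events; power 86.3%.

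The stated power reproduces and is not in dispute.

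**Inputs for the illustration.**
- From the protocol: 35% one-year deaths, taken as the SoC rate; 365 days of follow-up (Table 8); HR 0.90.
- Assumed, because the documents do not give them: the share f of included SoC patients who consent after time 0, and their lag L in years.
- Simplifications: constant hazards, and no censoring before one year. Table 8 also censors at the end of treatment, which is left out here.

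**Formulas.** The SoC hazard is λ = −ln(0.65) = 0.431 per year. A late consenter's one-year death probability is 1 − exp(−λ(1 − L)), and that patient's expected counted time is L + [1 − exp(−λ(1 − L))]/λ. The apparent HR is close to 0.90λ divided by (SoC deaths ÷ SoC person-years).

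**Worked case, L = 3 months.** A late consenter has death probability 1 − 0.65^0.75 = 0.276 and counted time 0.25 + 0.276/0.431 = 0.891 years. Other patients have 0.350 and 0.350/0.431 = 0.812 years.
- f = 25%: deaths 0.75 × 0.350 + 0.25 × 0.276 = 0.332; time 0.75 × 0.812 + 0.25 × 0.891 = 0.832; rate 0.398; apparent HR 0.388/0.398 = 0.97.
- f = 50%: deaths 0.313; time 0.852; rate 0.368; apparent HR 0.388/0.368 = 1.05.

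Solving the expected Cox score equation under the same assumptions (true HR 0.90, late consent in SoC only) gives:

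| Share of SoC consenting late | 1 month | 3 months | 6 months |
| --- | --- | --- | --- |
| 25% | 0.92 | 0.97 | 1.06 |
| 50% | 0.95 | 1.05 | 1.26 |
| 100% | 1.00 | 1.26 | 1.93 |

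At 25% and 3 months, with about 3,265 events, the chance of showing a benefit falls from 86% to about 12%.

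**Other branches.**
- Late consent in Drug A/B only (25%, 3 months), same formulas with hazard 0.90 × 0.431 = 0.388: deaths 0.304, time 0.847, rate 0.359; apparent HR 0.359/0.431 = 0.83, in favour of Drug A/B.
- Same share and lag in both arms: the HR stays at about 0.90.
- All consent on or before time 0: no bias.
- Risk time started at consent by delayed entry: 0.90 in every cell of the table.

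**The case against.** The strongest reply is that the protocol establishes neither premise. In the Table 2 sentence the consent clause sits with the patients given Drug A/B, and the controls are described only as treated with standard care. The Population row omits consent, as do Tables 4, 5 and 12, and Section 9 describes secondary use of routine-care data. The registry covers metastatic disease, and time 0 is the start of second- or third-line treatment, so registry consent could well come first. Retrospective inclusion may simply mean the historical arm, which the Table 10 contrasts do not use. Consent procedures may also be set out in the registry documentation, which is not available here.

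Most of this stands. A reader might infer that SoC survival is overstated and a benefit of Drug A/B hidden. The documents do not support that as fact: it needs controls to be bound by consent, consent to follow drug start, and Drug A/B patients not to be selected in the same way. The larger figures in the table are not estimates for this study.

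The reply does not settle the matter, however. If consent binds nobody, the objectives contradict the operational tables. If it binds only Drug A/B patients and follows drug start, the bias favours the new treatment. No reading assures that consent precedes time 0. The general disclaimer about items still to be discussed does not cover this, because Day 1 is stated as fixed and consent timing is not marked as open.

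**Conclusion.** The point holds conditionally. The objectives mention registry consent and retrospective inclusion, the follow-up rule starts everyone on Day 1, and nothing ties consent to time 0. If consent is a condition of inclusion and can follow drug start, the rule counts immortal time as time at risk.

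The bias goes against Drug A/B if late consent is mainly in SoC, in its favour if only Drug A/B patients must consent, and largely cancels if both arms share the same share and lag. The risk is clearest for the historical comparator. The primary contrast is affected only through 2021 to 2022 patients enrolled after drug start.

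The size cannot be known from the protocol. Under the stated assumptions, a 1-month lag in all SoC patients is enough to erase an HR of 0.90. Section 7.1 says only that the design helps prevent immortal time bias. That is a fair general statement, but it does not cover this route.

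**What to change.** 1. Reconcile the objectives in Table 2 with Tables 4, 5, 8 and 12: state whether consent is required, of which arms, and by when relative to time 0.
2. In Table 8, for all arms, start time at risk at the later of Day 1 and the consent date, using an entry-time variable in PHREG. This is unnecessary where consent falls on or before time 0, or where a waiver allows deceased patients to be included.
3. Report the index-to-consent interval by arm.

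The cost is one eligibility and follow-up line and one extra variable. Early person-time from late consenters is lost, and a patient whose on-treatment follow-up ends before consent contributes none. Delayed entry also assumes that, at a given time since drug start, consent timing is unrelated to prognosis. If all consent precedes time 0, the change alters nothing.
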